##### Parent interview

We will conduct semi-structured interviews with a sub-cohort of parents to enhance our understanding of financial distress, material hardship and financial coping behaviors among parents of children diagnosed with ALL. Study committee members trained in qualitative interviewing for research will conduct interviews by telephone or institution-approved remote platforms, per parent preference; a study committee member who is a bi-lingual ([name]), native Spanish speaker will interview parents who prefer to participate in Spanish. We expect interviews to last about 30 to 45 min, no matter the mode. The interview guide was informed by the conceptual model guiding the study (Fig. 1). Topics include: (a) distress related to financial costs, (b) how the parent approaches problem-solving and decision-making about financial coping behaviors, (c) whether someone has spoken with them about costs associated with ALL therapy and, if so, how the conversation went, and (d) what the parent would change for themselves or recommend to other parents regarding financial coping behaviors during childhood cancer therapy.

##### EHR extraction form

Participating sites will abstract clinically relevant information from the index child’s EHR at four time points. The first data will be entered at baseline and will include information from the Parent Information/Contact Form and the index child’s initial planned treatment regimen. Each subsequent clinical data abstraction form will guide the COG Research Coordinator in anticipated timing for subsequent surveys as well as inform sampling for the qualitative aim. The fourth and final clinical data abstraction form will classify the child’s final ALL risk classification, treatment regimen, and targeted healthcare utilization (emergency department visits, hospitalizations, and intensive care unit admission).

##### Institutional survey

Research personnel at each COG NCORP institution that enrolls at least one parent in this study will complete an annual survey about institution-level factors that may be associated with implementation of the recommendation for regular systematic financial distress screening of childhood cancer populations [29, 45]. The institutional survey includes items that ask about the availability of resources (social workers, financial advisors, navigators) for patients receiving care at the institution and their families. Survey items were adapted from a prior survey of pediatric oncology centers [46].

### Statistical considerations and analytic approach

#### Power calculation

We determined the sample size for aims 1 and 2 at 100, based on feasibility. Given the support for the reliability and validity of the PFWS provided by prior cross-sectional studies, we selected financial distress as measured by PFWS as our primary outcome. We expect to enroll parents in this study over a 2.5- to 3-year period, including a 6-month start-up period. Between 2010 and 2019, roughly 240 children per year diagnosed with ALL were enrolled onto treatment trials at the 47 COG institutions within the NCORP network. If half of these institutions activate this study, and 50% of eligible parents enroll, we estimate that 60 parents per year can be enrolled. Considering 10% attrition per year over 3 years, the study could enroll at least 100 parents within proposed accrual time. In a prior cross-sectional study of financial distress in cancer patients, [7] the PFWS mean score for patients under age 50 years was 5.0 (SD = 1.9); we expect that most parents who enroll in our proposed study will be young or middle-aged adults. In the prior study, for patients aged 50–64 years, the PFWS mean score was 5.7 (SD = 2.7) [7]. Assuming 100 parents enrolled and 73 complete the baseline survey plus one follow-up survey, we will have at least 90% power to detect a mean of paired differences of -0.5, with an estimated SD of paired differences of 1.3, and a significance level (alpha) of 0.050, using a two-sided paired t-test. We will have at least 80% power if the SD of paired differences is 1.5. These power calculations use estimates of SD for measurements at a single time point approximate to the results in Meeker et al. [7] not for differences in measurements from a baseline time point—these SDs are not readily available. We expect actual SDs of paired differences to be lower due to correlations between repeated observations, thus higher power in practice. A 0.5-point change in score is equivalent to 10% change in the mean 5.0 score from the Meeker study [7].

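### The SDs behind the stated 90% and 80% power (1.3 and 1.5) do not approximate the single-time SDs they are said to come from (1.9 and 2.7), so the claim that true power will be higher is unsupported

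*Protocol article*

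**What the plan says.** All the relevant statements are in the Power calculation section of the protocol article.

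- **Sample size.** The target of 100 parents is set by feasibility. Power is then worked out for the evaluable subset: "Assuming 100 parents enrolled and 73 complete the baseline survey plus one follow-up survey".
- **Test.** The setting is "a significance level (alpha) of 0.050, using a two-sided paired t-test".
- **Power.** The plan claims "at least 90% power to detect a mean of paired differences of -0.5, with an estimated SD of paired differences of 1.3", and adds: "We will have at least 80% power if the SD of paired differences is 1.5".
- **Prior data.** From one cross-sectional study of cancer patients it reports that "the PFWS mean score for patients under age 50 years was 5.0 (SD = 1.9"), and that "for patients aged 50–64 years, the PFWS mean score was 5.7 (SD = 2.7"). It expects most enrolled parents to be young or middle-aged.
- **Source of the SDs.** "These power calculations use estimates of SD for measurements at a single time point", described as approximate to that study's results and not as SDs of change from baseline, which are said not to be readily available.
- **Reassurance.** "We expect actual SDs of paired differences to be lower due to correlations between repeated observations, thus higher power in practice".

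**The concern.** The section gives 1.3 and 1.5 two descriptions. In the power statement they are SDs of paired differences. Two sentences later they are single-time-point SDs taken approximately from the prior study. The second description does not fit the figures printed beside it: 1.3 and 1.5 lie about 32% and 21% below 1.9, and further below 2.7. No within-parent correlation is given that would turn one kind of SD into the other.

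The reassurance depends on the second description. If 1.3 and 1.5 really were single-time SDs, correlation between repeated scores might bring the SD of the differences below them, and the stated power would be cautious. If the single-time SD is nearer 1.9, then 1.3 and 1.5 can be right only if the correlation is already strong, and the same correlation cannot also be counted as spare margin.

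The Personal Financial Wellness Scale (PFWS) score is the primary outcome and its change over time is Aim 1. A reader told that 90% is on the low side would take a null result as fair evidence against a 0.5-point change. The inputs the document quotes do not support that reading.

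**Working it through.** **Inputs, all from the Power calculation section:** n = 73 pairs; mean difference 0.5 in absolute value; two-sided alpha 0.05; paired t-test; SDs of differences 1.3 and 1.5; single-time SDs 1.9 and 2.7. The 73 agrees with 10% yearly attrition over 3 years: 100 × 0.9³ = 72.9. The within-parent correlation (rho) is not given, so it is treated as an assumption and varied.

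**Step 1: reproduce the stated power.** Exact power comes from the noncentral t distribution with 72 degrees of freedom and noncentrality (0.5 / SD of differences) × √73.

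- SD 1.3: noncentrality 0.5/1.3 × 8.544 = 3.29; power 90.0%.
- SD 1.5: noncentrality 0.5/1.5 × 8.544 = 2.85; power 80.2%.

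Both stated figures reproduce, so 1.3 and 1.5 were the inputs and the calculation was done correctly with them.

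**Step 2: use the quoted single-time SDs as the text describes.**

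- SD 1.9: noncentrality 0.5/1.9 × 8.544 = 2.25; power 60.2%.
- SD 2.7: noncentrality 0.5/2.7 × 8.544 = 1.58; power 34.5%.

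**Step 3: find what would link the two sets of SDs.** With equal SDs at both times, SD(diff) = SD × √(2(1 − rho)). This gives rho = 1 − SD(diff)² / (2 SD²).

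- From 1.9 to 1.3: 1 − 1.69/7.22 = 0.77.
- From 1.9 to 1.5: 1 − 2.25/7.22 = 0.69.
- From 2.7 to 1.3: 1 − 1.69/14.58 = 0.88.
- From 2.7 to 1.5: 1 − 2.25/14.58 = 0.85.

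**Step 4: test the reassurance.** SD(diff) is below the single-time SD only when √(2(1 − rho)) < 1, that is, when rho > 0.5. A positive correlation alone is not enough. At rho = 0.5 the two SDs are equal, so Step 2 is the same as assuming rho = 0.5.

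**Step 5: power over a range of correlations** (n = 73, difference 0.5):

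| rho | SD(diff) if SD = 1.9 | Power | SD(diff) if SD = 2.7 | Power |
|---|---|---|---|---|
| 0.5 | 1.90 | 60% | 2.70 | 35% |
| 0.6 | 1.70 | 70% | 2.41 | 42% |
| 0.7 | 1.47 | 82% | 2.09 | 52% |
| 0.8 | 1.20 | 94% | 1.71 | 69% |

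**Step 6: detectable difference.** Solving the Step 1 formula for the difference at n = 73 and SD(diff) = 1.9 gives 0.63 for 80% power and 0.73 for 90%, against the planned 0.50.

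**The case against.** The strongest reply is that nothing is miscalculated. The stated power follows from 1.3 and 1.5, the 80% figure is explicitly conditional on its SD, and the section admits that SDs of differences were not readily available. That stands: the fault lies in the stated origin of the inputs and the reassurance drawn from it, not in the computation.

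The second reply is that the sample size was fixed by feasibility, and that Aim 1 is analysed with a mixed model reporting a slope and 95% confidence interval, so imprecision will be visible. This also stands, and it limits the consequence: the number of parents does not rest on these SDs. It does not make the description of the inputs correct.

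Several stronger readings are tempting, but the documents do not support them:

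- **That the study's true power is 60% or 35%.** These are the results of using the quoted single-time SDs as the text describes, which amounts to rho = 0.5. At SD 1.9 and rho of 0.7 to 0.8, power is 82% to 94%, and nothing in the document rules that out.
- **That 35% deserves equal weight.** It uses the SD for ages 50–64. The 0.5-point effect is scaled to the under-50 mean of 5.0, so 1.9 is the more relevant benchmark and 35% is an outer bound.
- **That the correlation must be low because the surveys are more than two years apart.** That length is given for total treatment and bears at most on T1 to T3. No T1-to-T2 interval is stated, and either follow-up makes a parent evaluable.
- **That the authors knowingly counted the correlation twice.** The document does not say how 1.3 and 1.5 were chosen, and the prior study may report other SDs that it does not quote.

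**Conclusion.** The point holds as a mismatch between the stated source of the SDs and the SDs quoted. On the described basis, power at the more relevant SD of 1.9 is about 60%, not 90% or 80%. The stated figures are reachable, but only with a within-parent correlation of about 0.77 (for 90%) or 0.69 (for 80%) at that SD, or 0.88 and 0.85 at an SD of 2.7. Since none is stated, and correlation brings the SD of differences below the single-time SD only above 0.5, the expectation of higher power in practice is unsupported.

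This rests on n = 73, a 0.5-point difference, a two-sided 0.05 paired t-test, equal SDs at the two times, and the two SDs quoted in the article. It is a flaw in the power statement for the primary outcome. It does not show that the study is too small, and it leaves the derivation of the sample size untouched.

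**What to change.** Keep 100 enrolled and 73 evaluable, and rewrite the power basis:

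1. Label 1.3 and 1.5 as assumed SDs of paired differences, and state that they correspond to correlations of about 0.77 and 0.69 if the single-time SD is 1.9. If they came from another source, name it.
2. Report power over a range of correlations at SD 1.9 (60% at 0.5, 70% at 0.6, 82% at 0.7, 94% at 0.8), or give the detectable difference (about 0.63 at 80% power if the SD of differences is 1.9).
3. Delete the sentence presenting the inputs as single-time SDs, and the claim of higher power in practice.

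The cost is wording only. No parents are added and no analysis changes; the sole downside is a less favourable power statement.

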#### Analysis to address Aim 1: determine the trajectory of financial distress

We will compute PFWS scores using the established scoring algorithm [7, 35]. We will model continuous PFWS scores as a linear function of time; scores will be appropriately transformed to normality as necessary. We will fit a mixed model for mean PFWS score with an intercept and a main effect for time, as a categorical variable. We will use this model to examine the trend over time and estimate the slope of change (95% CI) in PFWS scores. We will consider parents with at least a baseline and an additional time point measurement (either T2 and/or T3) as evaluable. Research personnel will take steps in real time to ensure complete assessments and non-ambiguous responses. If missing data are unavoidable, we may explore alternative modeling assumptions.

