##### Parent survey

We designed the parent survey to include items that assess the following components of our conceptual model (Fig. 1): (a) socio-economic status (SES), (b) financial distress, (c) material hardship, and (d) financial coping behaviors. *Indicators of parent SES* to be measured directly by survey items or derived from the data include: the parent’s social relationship to the index child (mother, father, other guardian), household income, household structure (household size, headed by single-parent or not), parent education level, parent primary language, parent health literacy level as measured using a single-item, [30] parent employment status (e.g., fulltime, part-time, not employed), parent employment benefits (e.g., paid time off, sick leave), parent change in employment status, the index child’s insurance type at diagnosis, census-derived income quintile for the primary residence[34] and distance/travel time to treating institution (derived using residence and institution zip codes). Baseline survey is provided in Additional file 1.

We will measure *financial distress* with the 8-item Personal Financial Wellness Scale (PFWS), previously known as the InCharge Financial Distress and Financial Wellness Scale [35]. The PFWS has been used in prior studies to describe financial distress in adults with newly diagnosed solid tumors [7]. Items ask for the perspective of the respondent as the financially responsible individual using a 10-point response scale. Item responses are totaled and then divided by 8. Mean scores can range from 1 to 10, with 1 indicating overwhelming financial distress and 10 indicating no financial distress. All eight PFWS items have been shown to load onto a single latent factor, [36] providing support for the scale’s uni-dimensionality.

For this study, the first and second authors engaged with three independent certified professional translators (two forward translations reconciled into one document, back translation of the reconciled forward translations), and the Inclusive Science Team at the second author’s NIH-funded CTSA (UL1TR002489; PI: [name]) in using a best practices [36] to obtain a valid linguistic translation and cultural adaptation of the PFWS for use by parents who prefer to use Spanish in completing study measures.

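### The plan lets PFWS scores be transformed after the data are seen and does not keep the 1–10 scale, on which its own 0.5-point difference is set, for the primary Aim 1 estimate

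*Protocol article*

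**What the plan says.** The section on the Aim 1 analysis models PFWS as a continuous score and adds that "scores will be appropriately transformed to normality as necessary". The model is then given: "We will fit a mixed model for mean PFWS score with an intercept and a main effect for time, as a categorical variable". Its purpose follows: "We will use this model to examine the trend over time and estimate the slope of change (95% CI) in PFWS scores".

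The outcome is defined under Parent survey as the mean of eight items: "Mean scores can range from 1 to 10, with 1 indicating overwhelming financial distress and 10 indicating no financial distress".

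The Power calculation section works in the same untransformed points. With 73 of 100 parents evaluable, "we will have at least 90% power to detect a mean of paired differences of -0.5". This takes 1.3 as the SD of the change; for an SD of 1.5 the section gives a power of 80% or more. The size of the difference is explained in raw terms: "A 0.5-point change in score is equivalent to 10% change in the mean 5.0 score".

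No section says that the untransformed analysis stays primary if a transformation is made.

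**The concern.** Whether a transformation is needed can be judged only from the observed outcome, so the clause lets the scale of the primary estimate depend on the data. A non-linear transformation changes what is estimated. A 0.5-point change counts differently according to where the parent starts, so the transformation decides which parents drive the trend. The result would not be directly comparable with the difference used for power, or with PFWS means published in points. The Analytic considerations section rests the primary aim on a linear change over time, and linearity also depends on scale: a trend that is linear in points is generally not linear in logs.

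The clause may also be triggered without need. Inference on the time effect rests mainly on within-parent errors. Scores can look clearly non-normal because parents differ from one another, while the changes within parents behave well.

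**Working it through.** **1. The plan's own power figure.** Inputs from Power calculation: n = 73, difference 0.5, SD of paired differences 1.3 or 1.5, two-sided alpha 0.05, paired t-test. Non-central t with 72 df and non-centrality (0.5/SD) × √73:

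- SD 1.3: non-centrality 3.29, power 90.0% (stated: at least 90%).
- SD 1.5: non-centrality 2.85, power 80.2% (stated: at least 80%).

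Both figures reproduce. They are calculations in raw points, and keeping the raw scale leaves them unchanged.

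**2. What 0.5 points becomes after a transformation.** The article names none, so log(score) and log(11 − score) are assumptions, chosen as common options for right and left skew.

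| Fall of 0.5 from | change in log(score), absolute | change in log(11 − score) |
|---|---|---|
| 9 | ln(9/8.5) = 0.057 | ln(2.5/2) = 0.223 |
| 3 | ln(3/2.5) = 0.182 | ln(8.5/8) = 0.061 |
| ratio | 3.2, more weight to the parent at 3 | 3.7, more weight to the parent at 9 |

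Scores of 9 and 3 are fairly wide apart. At the reference mean ± 1 SD in Power calculation (5.0 ± 1.9, that is 6.9 and 3.1):

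- log(score): 0.075 and 0.176, ratio 2.3.
- log(11 − score): 0.115 and 0.061, ratio 1.9.

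**3. The reverse direction.** Fix the transformed change so that it equals −0.5 points at a score of 5.0.

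- log(score): ln(4.5/5) = −0.105, a 10% fall. This is −0.2 points at 2, −0.8 at 8 and −1.0 at 10.
- log(11 − score): ln(6.5/6) = 0.080. This is −0.75 points at 2, −0.25 at 8 and −0.08 at 10.

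No single transformed slope therefore stands for 0.5 points.

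**4. Direction can depend on the scale.** In a constructed case, half the parents move from 2 to 1.5 and half from 8 to 9. The mean raw change is (−0.5 + 1)/2 = +0.25. The mean log change is (ln 0.75 + ln 1.125)/2 = (−0.288 + 0.118)/2 = −0.085. This shows that a reversal is possible, not that it is likely.

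**5. Is transformation needed for valid inference?** Simulations with n = 73, no true change and an untransformed paired t-test:

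- Eight clipped integer items at two waves, 4,000 runs per scenario, mean skewness about −0.46, −0.78 and +0.62. Shapiro–Wilk rejected normality of the scores in 68%, 99% and 93% of runs. Type I error was 5.0%, 4.7% and 4.9%.
- Bimodal parent levels with normal within-parent errors, 20,000 runs. Type I error was 4.96%. In the 1,000 samples tested, Shapiro–Wilk rejected normality of the scores in 100% and of the paired differences in 6.5%.
- Exponential (extremely skewed) paired differences with SD 1.3, 20,000 runs. Type I error was 6.1%.

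A rule based on score normality would often call for a transformation that brings no benefit in type I error.

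**The case against.** The clause is conditional. By default the model, the mean score and the slope are all on the original scale, and the simulations suggest that a transformation would often not be needed. Which transformation, which diagnostic and what trigger are details that an article may leave to the full protocol or analysis plan. All of this stands. The point is therefore not that these details are missing, but that the stated rule lets the primary outcome be re-expressed.

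A reader might infer that the plan checks the wrong normality assumption. The article does not support this. It names no diagnostic, and it is the outcome that gets transformed even when residuals prompt the step. In a model with only an intercept and categorical time, normal residuals and random effects imply normal scores within each time point. Looking at scores is not irrelevant; they are just a poor trigger on their own.

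A reader might also infer that a transformed result could not be interpreted. That goes too far. Fitted values at T1, T2 and T3 can be back-transformed, and a log difference can be read as a percentage change, in line with the 10% wording in Power calculation. After a log, however, these are medians or geometric means and ratios. They are not directly mean changes in points, and step 3 shows that a fixed percentage is a different number of points at each score.

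Finally, the sample size of 100 rests on feasibility, and 0.5 is a detectable difference. It is not a success criterion or a minimal important difference. Transforming a skewed outcome is accepted practice, and the 6.1% under extreme skew shows that some safeguard is reasonable.

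**Conclusion.** The concern holds as a conditional one. As written, the plan allows the primary PFWS outcome to be transformed once the data are seen and does not keep an untransformed primary analysis. If that happens, the Aim 1 slope leaves the scale on which the score, the 0.5-point difference, the SDs and the power are stated, and it has no single equivalent in points. Under the assumed log and reflected log, the same 0.5-point fall differs 3.2-fold and 3.7-fold between scores of 9 and 3, in opposite directions. It differs about 2-fold between scores one SD either side of the reference mean.

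At n = 73 the untransformed comparison keeps about 5% type I error under moderate skew and about 6% under extreme skew, so little is lost by staying on the raw scale. It would be wrong to conclude that the power calculation is in error or that the slope will certainly be reported off scale; neither follows from the article. Severity is minor to moderate, and this is a cheap improvement.

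**What to change.** Replace the transformation clause in the Aim 1 analysis with wording to this effect: the primary estimate of change in PFWS and its 95% CI will be reported on the original 1–10 scale; model residuals will be examined; if they are clearly non-normal or heteroscedastic, robust (sandwich) or parent-level bootstrap confidence intervals will be given for the same changes in PFWS points; any model on a transformed scale will be reported as a sensitivity analysis only.

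The cost is a sentence or two of text and a standard software option. Sample size, data collection and the stated power do not change. The downside is that robust or bootstrap intervals may be slightly wider.

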#### Data collection

We will collect data from three sources: parents who enroll on study, the index child’s EHR, and institutions that enroll parents on study.

We will ask parents to complete a baseline (T1) and two follow-up (T2, T3) surveys over the course of the child’s treatment (respectively, during induction therapy, during maintenance therapy and then around the time of treatment completion). Parents of children whose ALL is refractory, relapses, or requires stem cell transplant or chimeric antigen receptor T-cell (CAR-T) will remain enrolled in the study if they have completed the T1 survey. These parents will be asked to complete one follow-up survey within 3 to 6 months of the child’s stem cell transplant or CAR-T therapy. Parents of children who die after the parent has completed the T1 survey will not be asked to complete follow-up survey(s) and will be removed from the study.

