### Participant retention and data quality considerations

We have a plan for close data monitoring and optimization of participant retention. We will identify missing parent survey data at the earliest possible time point, following the closure of the assessment window/expiration of survey link. We will run regular queries to identify missing assessments as well as missing data within the assessments. We will engage research personnel at the enrolling institution to assist us in determining the reason for missing assessments (e.g., illness, forgot, unable to make appointment). A study committee member will review completed surveys to identify missing items, and send reminders to parents and institutions via secure REDCap® link to encourage completion of missing items as soon as possible within the assessment window. If the T1 survey is missing, we will not include the parent in any analysis. However, if the T2 or T3 survey is missing, we will collect the reason for missing data with assistance from research personnel at the enrolling institution and may use the data as outlined in the statistical plan. We will also work closely through the NCORP network, including regular virtual meetings with COG research personnel at participating institutions, to discuss missing data and address challenges as proactively as possible. The NCORP network has been utilized in prior studies through COG and was successful in obtaining high-quality data.

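### Read as the analysis set, the Aim 1 evaluability rule and the exclusion of parents without T1 discard usable scores, so the mixed model loses its protection when dropout depends on T1 distress

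*Protocol article*

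**What the plan says.** Under the Aim 1 analysis heading, the protocol article specifies the model: "We will fit a mixed model for mean PFWS score with an intercept and a main effect for time, as a categorical variable". The same paragraph then defines who counts: "We will consider parents with at least a baseline and an additional time point measurement (either T2 and/or T3) as evaluable". It adds only that other modelling assumptions may be explored if missing data cannot be avoided.

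Three other places bear on the same set of parents:

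- Power calculation: "Assuming 100 parents enrolled and 73 complete the baseline survey plus one follow-up survey". The accompanying attrition assumption is "Considering 10% attrition per year over 3 years".
- Participant retention and data quality considerations: "If the T1 survey is missing, we will not include the parent in any analysis". If T2 or T3 is missing, the data may be used as the statistical plan sets out.
- Data collection: a parent whose child dies after the T1 survey "will not be asked to complete follow-up survey(s) and will be removed from the study". The text does not say what happens to surveys already returned.

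**The concern.** A likelihood-based mixed model uses partial records. If a parent answers T1 and then stops, the T1 score still informs the T1 mean and, through the within-parent correlation, the follow-up means. The estimated change stays valid as long as dropout depends only on scores that were observed. Restricting the fit to parents with T1 plus a follow-up gives this up: dropout must then be unrelated to T1 distress as well. Excluding parents without T1 also discards any T2 or T3 score they supply.

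A low score on the Personal Financial Wellness Scale (PFWS) means high distress. If parents with low T1 scores drop out more often, the retained T1 mean is too high, and regression to the mean then adds to the apparent worsening. If correlations between time points are equal, T2 and T3 shift by the same amount, so the artefact falls wholly on the T1-to-T2 interval. That matters in a study that hopes to locate inflection points.

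**Working it through.** **1. The plan's own figures.** Attrition: 100 × 0.9³ = 72.9, so 73 evaluable and 27 not. The plan claims "at least 90% power to detect a mean of paired differences of -0.5". Taking its difference SD of 1.3 and a two-sided test at 0.05, the noncentrality is (0.5/1.3) × √73 = 3.29 on 72 df, giving 90.0%. With SD 1.5 it is (0.5/1.5) × √73 = 2.85, giving 80.2%. Both stated powers reproduce. The issue is the analysis set, not the power.

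**2. Inputs for the illustration.**

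- From the Power calculation section: T1 mean 5.0 and SD 1.9 (cited study, patients under 50), target change −0.5, and 27% without a follow-up.
- Derived: the correlation ρ between T1 and follow-up. With equal SDs, ρ = 1 − SD_diff²/(2 × 1.9²). SD_diff 1.3 gives 1 − 1.69/7.22 = 0.77; SD_diff 1.5 gives 1 − 2.25/7.22 = 0.69.
- Assumed, not in the document: all 27% completed T1; dropout is logistic in the T1 score, with odds ratio (OR) 1.5, 2 or 3 per SD lower score; one follow-up; bivariate normal scores. ρ = 0.5 is added as a wider case.

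**3. Formula.** If the retained T1 mean is too high by D, the follow-up mean is too high by ρD, so the change is biased by −(1 − ρ)D.

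**4. Dropout driven by the T1 score** (simulation of 2 million pairs, true change −0.50). The retained T1 mean is 5.20 at OR 1.5, about 5.33 at OR 2 and about 5.47 at OR 3, against a true 5.00. Estimated change in the evaluable-only set:

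| ρ | OR 1.5 | OR 2 | OR 3 |
|---|---|---|---|
| 0.77 | −0.55 | −0.58 | −0.61 |
| 0.69 | −0.56 | −0.60 | −0.64 |
| 0.5 | −0.60 | −0.66 | −0.73 |

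The formula agrees: 0.23 × 0.20 = 0.05 at the low end for ρ = 0.77, and 0.31 × 0.46 = 0.14 at the high end for ρ = 0.69. Against the 0.5-point target these are 0.05/0.5 = 10% and 0.14/0.5 = 28%. At ρ = 0.5 the largest bias is 0.23. The likelihood estimate that keeps all T1 scores is the responders' follow-up mean, plus the regression slope times (all-parent T1 mean − responder T1 mean), minus the all-parent T1 mean. It returns −0.50 in every cell.

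**5. Other mechanisms.** With dropout unrelated to distress, both sets give −0.50. With dropout driven by the unseen follow-up score (same odds ratios, all three correlations), the evaluable-only set gives −0.26 to −0.45 and the all-T1 set −0.14 to −0.42. Both understate the decline, and the all-T1 set is further from the truth.

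**The case against.** **The word evaluable may be only a count.** The article never says that T1-only scores leave the fit, and the retention section leaves the use of data with a missing T2 or T3 to a statistical plan that is not shown. This stands as a caveat. However, the definition sits inside the Aim 1 analysis paragraph and matches the 73 in the power calculation, and the exclusion of parents without T1 is explicit. If only a count was meant, one sentence settles it.

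**The size is easily overstated.** A reader might infer that 27% of baseline data will be lost. The 27 are enrolled parents, and any who never returned T1 have no score to discard. They also reflect three full years of attrition, whereas evaluability needs only T2. So 27 of 100 is an upper bound. A bias of 0.23 needs ρ = 0.5, which implies a paired-difference SD of √(2 × 1.9² × 0.5) = 1.9, against the plan's 1.3 to 1.5. At the planned correlations the bias is below one standard error (1.3/√73 = 0.15). That does not excuse it, because it is systematic and avoidable, but it is moderate.

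**The direction is not settled.** A reader might infer that the rule must exaggerate the decline because the most strained parents stop responding. The document gives no evidence on who drops out. Strain felt at follow-up would reverse the sign, and widening the analysis set would not help.

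**Child death, relapse and Aim 2.** A reader might infer that bereaved parents' completed surveys are deleted. The sentence ends contact and does not say that; a parent bereaved after T2 still meets the evaluability rule. Parents of children with relapse, transplant or CAR-T stay enrolled with one follow-up survey. The evaluability sentence is not repeated under Aim 2, so carrying it over is an inference.

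**Prevention is planned.** Real-time checks, queries and collection of reasons should reduce missing data, but they do not determine how the remainder is analysed.

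**Conclusion.** The concern holds in a conditional form. Taken as the analysis set, the stated rules discard T1-only scores (up to 27 of 100 enrolled parents) and any T2 or T3 scores without T1. They thereby give up validity when dropout depends on observed T1 distress, with no inferential gain in return.

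Under that mechanism, and with the plan's own SDs, the T1 mean is about 0.2 to 0.5 points too favourable and the decline is overstated by about 0.05 to 0.14 points, rising to about 0.23 if ρ is 0.5. These figures rest on the assumed 27% T1-only share and odds ratios of 1.5 to 3. The effect of excluding parents without T1 cannot be sized from the document.

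A certain direction of bias, a 27% loss of baseline data, and deletion of surveys after a child's death are not supported. The plan should be changed, but the flaw does not invalidate the study.

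**What to change.** 1. Fit the Aim 1 mixed model by restricted maximum likelihood to all enrolled parents with at least one PFWS score (T1, T2 or T3), use the same set for Aim 2, and amend the sentence that excludes parents without T1.
2. Keep T1 plus one follow-up as the basis for power and as a sensitivity analysis.
3. Pre-specify a sensitivity analysis for informative dropout, for example shifting the unobserved follow-up scores of dropouts over a stated range. Step 1 does not deal with dropout that depends on the unseen score.
4. State that removal after a child's death ends follow-up and that surveys already completed are retained.

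The cost is a few sentences and a little extra analysis. No new data are needed, and the article reports that none had been captured when it was written.
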